### Sample recruitment: inclusion and exclusion criteria

2.9

Inclusion and exclusion criteria for the study is shown in Table 1. Female teachers of selected public secondary schools meeting the inclusion criteria will be approached and those consenting to be a part of the study will be recruited.

**Table 1 tab1:** Inclusion and exclusion criteria.

Inclusion criteria	Exclusion criteria
Females aged 30 to 45 years of age.	Female teachers who are undergoing any medicinal, herbal, or nutritional therapies.
Females who have not been medically diagnosed with a non-communicable disease.	Pregnant and breastfeeding females.
Females who have one or more of the non-communicable disease risk factors: BMI > 25 kg/m^2^ Waist circumference > 88 cm Fruit and vegetable intake < 5 servings per day Physical activity < 150 min/week	Female teachers who will not be staying in the school for the next 9 months

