### Duration of study

2.4

The study will be conducted over a period of 17 months and the timeline will be as follows:

Phase 1 - Baseline data collection – 02 months.

Phase 2 - Intervention development and implementation

Phase 2a - Planning and adaptation of interventions − 02 monthPhase 2b - Pre-testing the intervention − 02 monthsPhase 2c - Intervention implementation − 09 months

Phase 3 - Evaluation of intervention impact − 02 month.

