### Data collection techniques

2.10

Data collection will be done using validated and pre-tested questionnaires, designed specifically to obtain data on non-communicable disease risk factors and dietary and physical activity adherence levels. These questionnaires will be administered through face to face surveys where the researcher will distribute the questionnaires to the study participants and guide them on how to fill them. Researcher will take the body measurements of the subjects for anthropometric data and glucometers and cholesterol test kits will be employed to get biochemical parameter data.

The questionnaires will be administered in the 1st and 3rd phase of the study to get a baseline and evaluative risk factor assessment. Female teachers will be approached in their place of employment and once they have given consent to be a part of the study they will be asked to fill in the questionnaires. The participants will be briefed prior to questionnaire administration so that they may be able to understand what is being asked and how to best answer it.

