The proposed study has several limitations that need to be acknowledged. Firstly, purposive sampling of urban school may introduce sampling bias, thereby limiting generalizability of results beyond urban, middle-income employed females. Secondly, while baseline data will be collected for both control and intervention groups to establish baseline equivalence, the lack of multiple data collection points may weaken the parallel trends assumption. While multiple regression modeling and where needed, propensity score weighting will be employed to adjust for noticeable differences, the potential for residual confounding still exists. Thirdly, while anthropometric indicators will provide significant insights into participant NCD risk profile, lack of biochemical indicators may limit the study’s ability to assess subclinical physiological changes post-intervention. Fourth, the reliance on self-reported KAP measures may include social desirability bias, particularly in the intervention group after exposure to educational material. Lastly, steps will be taken to standardize intervention delivery and fidelity monitoring, variation in participant engagement may affect consistency of intervention outcomes.

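### The stay-in-school criterion covers 9 months, but baseline to end-line takes 13 to 17 months, so teachers already known to be leaving before end-line are eligible

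*Protocol article*

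**What the plan says.** Table 1 (section 2.9) lists among the exclusions "Female teachers who will not be staying in the school for the next 9 months". It does not say from which date the nine months run.

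Section 2.4 states: "The study will be conducted over a period of 17 months". The phases listed there are:

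- baseline data collection, 2 months ("Phase 1 - Baseline data collection – 02 months")
- planning and adaptation, 2 months
- pre-testing ("Pre-testing the intervention"), 2 months
- implementation, 9 months ("Intervention implementation − 09 months")
- evaluation, 2 months

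Section 2.7.2 decides eligibility by STEPS screening. Section 2.10 places consent before the questionnaires and fixes when outcomes are collected: "The questionnaires will be administered in the 1st and 3rd phase of the study to get a baseline and evaluative risk factor assessment".

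Section 2.8 allows 10% for non-response and arrives at 65 teachers per group. Section 2.2.2 has the control group assessed at the same time points as the intervention group. Section 2.1 names difference-in-differences (DID) as the design. Section 2.14.2 also plans paired t-tests and McNemar tests of pre against post values.

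**The concern.** The nine months in Table 1 equal the length of the intervention phase. Eligibility, however, is settled at recruitment, and four months of planning and pre-testing come between baseline and the first session. A criterion meant to keep teachers who will be present throughout therefore expires before outcomes are collected. For example, a teacher who knows at screening that she will transfer in study month 12 passes Table 1, although by then she will have left the school where the sessions take place.

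At stake is loss that could have been prevented at screening, in a study whose sample size has no margin beyond the 10% allowance.

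The same calendar has a second consequence. Baseline is taken 4–6 months before the first session, so any simple before–after comparison spans a stretch in which no intervention was given.

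**Working it through.** **Calendar (section 2.4).** 2 + 2 + 2 + 9 + 2 = 17 months. This reproduces the stated total, and does so only if the phases run one after another. Baseline is then in months 0–2, planning 2–4, pre-testing 4–6, intervention 6–15 and end-line 15–17.

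**Intervals that follow.**

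- Baseline to first session: 6 − 2 = 4 to 6 − 0 = 6 months.
- Baseline to end-line: 15 − 2 = 13 to 17 − 0 = 17 months.

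**Reading A: nine months counted from recruitment (months 0–2).**

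- The window ends at 0 + 9 = month 9 to 2 + 9 = month 11.
- Intervention months covered: 9 − 6 = 3 to 11 − 6 = 5 of 9, so 4–6 are uncovered.
- Gap to end-line: 15 − 11 = 4 to 17 − 9 = 8 months.

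**Reading B: nine months counted from the first session (month 6).**

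- The window ends at 6 + 9 = month 15, when end-line starts.
- Uncovered: 15 − 15 = 0 to 17 − 15 = 2 months.

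**Sample size as planned (section 2.8).** n = 2σ²(z₁₋α/₂ + z₁₋β)²/d², with σ = 0.96, d = 0.5, two-sided α = 0.05 and power 80%:

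- 2 × 0.9216 × (1.960 + 0.842)² / 0.25 = 57.87, rounded up to 58.
- 58 / 0.90 = 64.4, rounded up to 65 per group. The plan's figure is reproduced.

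**Extra loss.** The article gives no turnover rate. The range of 5–15% a year is an assumption.

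- Reading A: 4/12 × 5% = 1.7 points to 8/12 × 15% = 10 points.
- Reading B: at most 2/12 × 15% = 2.5 points.

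These are upper bounds on what the criterion could prevent, because they count every leaver and not only those who know at screening that they will go.

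**Power under the plan's formula.** Power = Φ(d / (σ√(2/m)) − 1.960), with m teachers per group retained out of 65:

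| Total loss | m per group | Power |
|---|---|---|
| 10% (planned) | 58.5 | 80.4% |
| 12% | 57.2 | 79.5% (79.4% at 57) |
| 12.5% (upper end of reading B) | 56.9 | 79.3% |
| 15% | 55.2 | 78.2% |
| 20% (upper end of reading A) | 52.0 | 75.7% |

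On the same assumptions, holding 80% power would need 69 per group at 15% loss and 73 at 20%.

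**Pre-session change.** Let c be a change between baseline and the first session that is common to both groups, and x an additional change in the intervention group only. A before–after comparison within the intervention group is off by c + x. The DID contrast is off by (c + x) − c = x, so it is unaffected when x = 0.

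**The case against.** The strongest defence is that the sponsor meant the nine months of the intervention. Table 1 does not say so, and *the next* nine months, in a criterion applied at recruitment, reads more naturally as starting then. The starting point is nevertheless undefined, so both readings are given above. The defence shrinks the gap but does not close it, because even reading B stops as end-line opens.

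It is also fair to say that the loss of power is modest, that it rests on an assumed turnover, and that only part of it could be avoided. All of that stands.

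A reader might infer three stronger things that the article does not support:

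- **That pre-session drift, or regression to the mean after risk screening, is counted as intervention effect in the main contrast.** Both groups pass the same risk screen and are measured at the same times, and the design is DID, so change common to both cancels. Only differential change would bias it. The article offers no evidence of such change and already concedes that "the lack of multiple data collection points may weaken the parallel trends assumption". Sections 2.1 and 3 add regression adjustment and, where needed, propensity score weighting.
- **That a teacher who moves school cannot give an end-line measurement.** Nothing says movers are dropped. How they are followed up may be set out in the full protocol.
- **That the loss will differ by arm.** This is not shown, and section 2.2.2 plans monitoring visits to control schools to limit attrition.

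**Conclusion.** The stated criterion conflicts with the stated calendar: nine months are required where baseline to end-line takes 13–17. The uncovered time is 4–8 months if the nine months run from recruitment and 0–2 months if they run from the first session. The first range assumes sequential phases, which the 17-month total requires, and eligibility decided around Phase 1, which sections 2.7.2 and 2.10 indicate.

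The consequence is a risk of avoidable loss beyond the 10% allowance, of unknown size. At an assumed 5–15% yearly turnover the upper bound is about 2–10 points, giving power of about 79–76% against 80%. On the second reading it is at most 2.5 points, or about 79% power. This is a modest problem, worth correcting because the correction is so cheap.

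The timing of baseline is a secondary matter. It affects the paired t-test and McNemar comparisons, which take in 4–6 months of pre-session change and any regression to the mean. It does not undermine the DID contrast where the change is common to both arms.

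**What to change.** Reword the exclusion in Table 1 to: *not expected to remain in the school until completion of the end-line assessment (study month 17)*. This also removes the doubt about the starting point. The cost is one table cell and slightly fewer eligible teachers.

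State in section 2.14.2 that the claim of effect rests on the DID contrast, and that the paired t-test and McNemar results are descriptive of change within each group. This costs one sentence.

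Optionally, repeat weight, waist and hip just before the first session. That would give those measures a baseline next to the intervention and a second pre-intervention point for looking at parallel trends. It needs another measurement round in about 8 schools and would not refresh the diet, activity or awareness outcomes. The first two changes do not depend on it.

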### Data collection techniques

2.10

Data collection will be done using validated and pre-tested questionnaires, designed specifically to obtain data on non-communicable disease risk factors and dietary and physical activity adherence levels. These questionnaires will be administered through face to face surveys where the researcher will distribute the questionnaires to the study participants and guide them on how to fill them. Researcher will take the body measurements of the subjects for anthropometric data and glucometers and cholesterol test kits will be employed to get biochemical parameter data.

The questionnaires will be administered in the 1st and 3rd phase of the study to get a baseline and evaluative risk factor assessment. Female teachers will be approached in their place of employment and once they have given consent to be a part of the study they will be asked to fill in the questionnaires. The participants will be briefed prior to questionnaire administration so that they may be able to understand what is being asked and how to best answer it.

### Data collection tools

2.11

The following two tools will be used to collect data:

#### ‘WHO STEP wise approach to non-communicable disease risk factor surveillance (STEPS) questionnaire’

2.11.1

The STEPS questionnaire is divided into 3 sections:

STEP 1 – demographic and behavioral risk factor assessment such as age, gender, education, employment status, as well as health assessment such as dietary intake data, physical activity assessment, and disease, specifically NCD history.STEP 2 – anthropometric assessment including body measurements such as weight, height, waist circumference, body mass index (BMI).STEP 3 – biochemical assessment including blood tests for glucose, cholesterol and lipid levels.

In our study, the questionnaire will be adapted to include only the first two steps and not biochemical assessment due to funding restraints.

#### General knowledge and attitudes related to non-communicable diseases (GK), NCD behavioral risk factors (RF), and different NCDs

2.11.2

It was developed and validated by Yenit et al. will be adapted (42). It assess knowledge across three NCDs: diabetes mellitus, hypertension, and cardiovascular diseases (CVDs). Each disease section has its own maximum knowledge score: 22 points for diabetes, 10 points for hypertension, and 22 points for cardiovascular diseases. Additionally, overall knowledge scores will be interpreted using tertile cut-offs. Scores less than 33rd percentiles will be considered low knowledge, 33^rd^ to 66^th^ percentile will be moderate knowledge and more than 66th percentile will be termed high knowledge scores. The general knowledge and attitudes regarding NCDs set the basis for developing them in later years. Studies have focused on collecting data on different population group’s knowledge regarding NCDs but there remains a gap in associating this knowledge with the risk of developing NCDs. Our study aims to address this by associating the level of NCD related knowledge and attitudes with the behavioral and anthropometric risk factors of NCDs. Furthermore, our study’s population is urban female educators and gauging their knowledge and attitudes can help us get a deeper insight into the NCD related knowledge in urban women. A Malaysian study found that rural respondents had better NCD attitudes and practices as compared to the urban population, whereas there were no significant differences in NCD knowledge. Additionally, despite urban population having greater knowledge regarding NCDs, their attitudes and practices remained unsatisfactory (43). This calls for NCD awareness interventions in the urban population groups, which is also the basis for our study’s intervention. A Zimbabwean study found 65% of the study participants to be knowledgeable about NCDs and 81% reported good perceptions about these diseases. These results were significantly influenced by age, gender, and education level of respondents, with females being 1.8 times, those ages 40 years and above being 0.1 times and those with primary education level being 0.2 times more likely to have better perception of NCDs (44).

#### National Knowledge, attitudes and practices survey on non-communicable diseases

2.11.3

The data for the third outcome variable will be collected using the ‘National Knowledge, Attitudes and Practices Survey on Non-Communicable Diseases’ developed and validated by Demaio et al. (45) will be adapted to assess the participants’ knowledge, attitude and practices regarding the NCDs and their risk factors at both baseline and end-line assessment. It uses a combination of likert scale, true/false, and multiple choice questions to assess knowledge, attitudes and practice scores. The knowledge items are scored as correct = 1 and incorrect/do not know = 0. Attitude items are scored on a likert scale as strongly disagree = 1 to strongly agree = 4, and are coded in reverse where necessary. Practice items are scored as healthy behavior = 1 and unhealthy/risky behavior = 0. Domain specific scores are summed and categorized in low, moderate and high based on established tertiles or study specific score distribution.

#### Focus group discussions

2.11.4

Focus group discussions will be carried out with female teachers. An interview guide will be developed and validated to collect data from participants regarding the barriers and facilitators for their adoption of lifestyle changes/adherence. A total of 4 groups comprising of 6–8 participants each will be conducted. Therefore, 24–32 participants will be selected for focus group discussions. Both intervention and control group participants will be stratified to get differential perspectives on the intervention. Additionally, 10–12 in-depth interviews will be conducted with school principals and teachers. This will provide deeper insight into the barriers and facilitators to lifestyle change at the individual and administrative levels. Participants will undergo purposive selection to ensure maximum variation in age, teaching experience, socio-economic status, and other socio-demographic variables. The final number of focus groups and interviews will be determined by data saturation point, where no further themes emerge.

### Study outcomes

2.12

#### Primary outcomes

2.12.1

The primary outcomes of the study include body mass index (BMI), dietary and physical activity behaviors, and NCD awareness (44).

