**Methods:**

A quasi-experimental mixed methods study will be conducted in public secondary schools of Islamabad city, Pakistan, including both an intervention and control group. The study will be divided into three phases; baseline assessment, intervention development and implementation, and an end-line assessment. Comparisons will be made between control group and intervention groups, as well as pre and post intervention. Following the end-line assessment, in-depth interviews will be conducted on a sample of teachers to explore the barriers and facilitators to adoption of lifestyle changes. A total of 130 teachers, recruited through purposive sampling, will be divided into 2 groups of 65 in intervention and control groups each. The intervention will span 9 months, and consist of bi-weekly education and training sessions on lifestyle modifications. The sessions will include topics relevant to nutrition and physical activity, and take home resources such as sample menus, list of healthy food options etc. Primary outcomes of the study include anthropometric measurements including weight, body mass index (BMI), waist and hip circumference (WHC), waist to hip ratio (WHR). Secondary outcomes will include knowledge and awareness of NCDs and their associated risk factors.

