### Sample size calculation

2.8

The sample size is calculated on the basis of BMI reported from a similar study conducted in India (41) using the formula: $n=[2\times (\sigma^{2})\times {\left(Z₁-\alpha /₂+Z₁-\beta \right)}^{2}]/d^{2}$

Where SD = 0.96.

Alpha = 0.05.

Power of study = 80%.

Effect size = 0.5.

Non-response rate = 10%.

Sample size = 65 per group and total sample = 130 teachers (both groups).

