#### Secondary outcomes

2.12.2

The secondary outcomes for the study include anthropometric measures including waist circumference (WC), hip circumferences (HC), waist to hip ratio (WHR), and waist to height ratio (WhTR), and NCD risk factors awareness (45).

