#### Inferential statistics

2.14.2

Paired samples t-test will be used to compare the pre and post intervention values of continuous variablesMcNemar test will be used to compare the pre and post intervention values of categorical variablesChi-square test will be applied to determine associations between different variablesRegression analysis will be conducted to estimate the direction and strengths of relationships between independent and dependent variablesTo adjust for potential confounders such as socio-demographic variables, multivariable regression models will be employed. Variables such as age, household income, education level, will be included as covariates in the DiD analysis. This will help adjust for baseline differences between control and intervention groups, ensuring more accurate attribution of the intervention’s effects. This further enhances the internal validity of the study via limiting confounding bias.To control the risk of type I error, statistical corrections will be applied for multiple comparisons, where appropriate. This will include Bonferroni correction and/or false discovery rate (FDR) correction.

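### The abstract and section 2.12 name contradictory primary outcomes; only BMI is primary in both, and only BMI is sized

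*Protocol article*

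**What the plan says.** The protocol article defines its outcomes twice.

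- **Abstract, Methods, primary:** "Primary outcomes of the study include anthropometric measurements including weight, body mass index (BMI), waist and hip circumference (WHC), waist to hip ratio (WHR").
- **Abstract, Methods, secondary:** "Secondary outcomes will include knowledge and awareness of NCDs and their associated risk factors".
- **Section 2.12.1, primary:** "The primary outcomes of the study include body mass index (BMI), dietary and physical activity behaviors, and NCD awareness".
- **Section 2.12.2, secondary:** "The secondary outcomes for the study include anthropometric measures including waist circumference (WC), hip circumferences (HC), waist to hip ratio (WHR"), followed by waist-to-height ratio and awareness of NCD risk factors.

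Section 2.8 sizes one outcome: "The sample size is calculated on the basis of BMI reported from a similar study conducted in India", with SD 0.96, alpha 0.05, 80% power, "Effect size = 0.5" and 10% non-response, giving 65 per group.

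Section 2.14.2 says that multiple comparisons will be corrected where this is suitable, and adds: "This will include Bonferroni correction and/or false discovery rate (FDR) correction". The article does not rank the primary outcomes or say whether one or all of them must succeed.

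**The concern.** The two lists cannot both be right. The waist and hip measures change tier between them, and so does awareness. A reader therefore cannot tell which result the study will stand on. If waist falls and BMI does not, the abstract supports a positive primary finding. If awareness rises and BMI does not, section 2.12.1 does.

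The awareness case matters most. The limitations paragraph of the Discussion accepts that self-reported knowledge, attitude and practice measures are open to social desirability bias, above all in the group that receives the teaching. An outcome that the authors themselves expect may lean towards the intervention is secondary in one place and primary in another.

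The sample size adds a second difficulty. It rests on BMI alone at the full 0.05, with no allowance for sharing that error rate among several primaries.

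**Working it through.** **1. The lists side by side**

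| Outcome | Abstract | Section 2.12 |
|---|---|---|
| BMI | primary | primary |
| Weight | primary | absent |
| Waist, hip, waist-to-hip ratio | primary | secondary |
| Waist-to-height ratio | absent | secondary |
| Dietary and activity behaviours | absent | primary |
| NCD awareness | secondary | primary |
| Awareness of risk factors | secondary | secondary |

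BMI is the only outcome that is primary in both. Section 2.12 also splits awareness across the two tiers.

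**2. The plan's own sample size**

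Inputs are from section 2.8, with 0.5 read as an absolute BMI difference.

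n = 2 × 0.96² × (1.960 + 0.842)² / 0.5² = 57.87, so 58 evaluable per group.

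58 / 0.9 = 64.4, so 65 per group. The stated figure reproduces. Reading 0.5 as a standardised effect gives 63, or 70 after inflation, which does not match.

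**3. BMI power if Bonferroni is applied across m primary outcomes**

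Power ≈ Φ(0.5 / (0.96 × √(2/n)) − z), where z is the two-sided critical value at 0.05/m. The first term is 2.805 at n = 58 and 2.969 at n = 65.

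The value of m is an assumption. Section 2.12.1 gives three outcomes if diet and activity count as one and four if they are separate. The abstract gives four, or five if waist and hip are separate.

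| m | alpha per test | Power, 58 per group | Power, 65 per group | Evaluable per group for 80% | After 10% non-response |
|---|---|---|---|---|---|
| 1 | 0.05 | 80.1% | 84.4% | 58 | 65 |
| 3 | 0.0167 | 65.9% | 71.7% | 78 | 87 |
| 4 | 0.0125 | 62.1% | 68.1% | 83 | 93 |
| 5 | 0.01 | 59.1% | 65.3% | 87 | 97 |

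Under the Benjamini-Hochberg procedure the threshold that BMI meets lies between 0.05/m and 0.05, depending on the other p-values. At 58 per group its power therefore lies between roughly the Bonferroni figure and 80%.

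**4. If no correction is applied**

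The chance of at least one false positive among m independent tests at 0.05 is 1 − 0.95^m:
- m = 3: 1 − 0.857 = 14.3%
- m = 4: 1 − 0.815 = 18.5%

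Positive correlation lowers these figures. Steps 3 and 4 are alternatives and cannot both apply. None of these figures allows for clustering by school or for covariate adjustment.

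**The case against.** The strongest reply is that the article commits to correcting for multiplicity, and that the family, the number of tests and the exact method are normally settled in an analysis plan, which is not shown here. That largely stands, so the open family and method are not charged as a separate error. It does not help with the two lists: an analysis plan cannot make both of them true.

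A reader might infer that the plan has promised Bonferroni and so has already given up its 80% power. Section 2.14.2 does not support this. Correction is conditional and may be by false discovery rate, so the loss is certain only if several primaries are kept and Bonferroni is chosen.

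A reader might also compute 1 − 0.95^5 = 22.6% for five primaries in the abstract. That needs independence, which cannot hold there: with adult height essentially fixed, BMI is rescaled weight, and waist-to-hip ratio is built from two other items on the list.

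It is also fair to say that awareness and practices are stated aims in the Introduction, so making them secondary is a real choice. Finally, nothing in the article shows an intention to pick the favourable set. The point is that the text as it stands would permit it.

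**Conclusion.** The contradiction holds on the face of the document and needs no assumption. Outcomes other than BMI change tier or drop out between the abstract and section 2.12, and BMI is the only outcome that is both common to the two primary lists and sized.

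The numerical consequences are conditional:

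- **Several primaries with Bonferroni:** BMI power is about 66%, 62% or 59% for three, four or five outcomes with 58 evaluable per group, and 72%, 68% or 65% if nobody is lost.
- **False discovery rate control:** between roughly those figures and 80% at 58 per group.
- **No correction:** 14.3% to 18.5% for three to four independent outcomes, and less with correlation.

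If success required every primary outcome to be significant, alpha would not need dividing, but joint power would then be unaddressed. The article states no such rule.

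This should be corrected before endline results are seen, because a later choice of primary would look driven by the data.

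**What to change.** Make the abstract and sections 2.12.1 and 2.12.2 identical. Name change in BMI as the single primary outcome, tested at two-sided 0.05. The stated 80% power and 65 per group then remain valid on their own inputs. List weight, waist, hip, waist-to-hip ratio, waist-to-height ratio, diet, activity and awareness as secondary. In section 2.14.2, replace the open choice with one named correction for that secondary family, for example Holm or a false discovery rate method.

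The cost is wording in the abstract and sections 2.12.1, 2.12.2 and 2.14.2, with no change to recruitment. The real downside is that behaviour and awareness, which are stated aims, lose primary status. If the sponsor prefers to keep them as co-primaries, it should fix the number of outcomes and the method and restate BMI power at the divided alpha. Holding 80% under Bonferroni would take about 87, 93 or 97 recruited per group for three, four or five outcomes.
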